## Number of Participants

The aim is to enrol 150 patients into the study but sites will be allowed to recruit until a maximum of 200 patients are enrolled.

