## Participant Population

This study will be conducted at 4 sites in Australia at which the CDM model of caring for patients with cirrhosis has not been instigated. Participants will be from inpatient admissions where patients have come into hospital with a symptom of decompensation.

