# Statistical Methods

## Sample size and power analysis

The trial will be powered for the primary endpoint of unplanned liver-related admissions. Assuming an admission rate of three admissions per person per year in the usual care group, and a reduction of 20 % in the treatment group, a sample size of 146 (50 per site) would provide 80% power to detect a significant difference in event rates between groups at a type 1 error rate of α=0.05. This assumes a median follow-up time of 18 months, as well as allowing for a 20% attrition rate throughout the trial. Recruitment of a sample size of 147 patients within 12 months is feasible and represents approximately 38 patients per site. The anticipated caseload of intervention patients per site is 19, which was less than the caseload during the pilot trial (40) and will be feasible with a 0.6 fte RN level 3 nurse at each site.

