# Trial Management

## Training

To optimize implementation, a two-day training workshop will be held for the four CLD nurses employed by the trial. The workshop will be run by [name], [name] and [name], who developed extensive experience in CLD CDM practice during the pilot. The aims of the workshop will be to familiarize nurses with CLD medical management protocols, standardize nursing approaches to CDM, and research processes and data collection requirements. Data entry will be centralised and double key verification will be included. Consistency checks will be incorporated into the data entry procedure. Principal Investigators from each site will also join for a morning of training about the study requirements, medical protocols and data collection requirements.

All investigators will teleconference initially monthly to oversee quality management and timeline issues related to the project. In addition, a Project Management Executive involved in the day-to-day management ([name], [name], [name] and CLD nurses at SCGH, QEH, LMH, and RAH) will initially teleconference weekly for the first two months, then fortnightly-monthly throughout the duration of the project. The trial managers ([name]) will be responsible for operational management of the trial and [name] will be responsible for data entry and randomisation and will remain separate from day-to-day management.

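### The sample-size paragraph gives 146 patients as 50 per site, but at the four stated sites that is 200 patients; 146 to 150 patients is about 37 per site

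*Protocol*

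**What the plan says.** The Protocol, under Sample size and power analysis, says that "a sample size of 146 (50 per site") gives 80% power for a 20% reduction from three unplanned liver-related admissions per person per year. It assumes a median follow-up of 18 months and allows for 20% attrition. The same paragraph continues: "Recruitment of a sample size of 147 patients within 12 months is feasible and represents approximately 38 patients per site". It then argues staffing: "The anticipated caseload of intervention patients per site is 19, which was less than the caseload during the pilot trial (40"), and calls this workable with 0.6 fte of a nurse at each site.

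The number of sites is fixed elsewhere. Participant Population says "This study will be conducted at 4 sites in Australia", Training says "a two-day training workshop will be held for the four CLD nurses employed by the trial", and the Baseline Collection Tool (Appendix A) numbers four hospitals 1 to 4. Number of Participants sets an aim of 150 and adds that "sites will be allowed to recruit until a maximum of 200 patients are enrolled". Randomization, stratification, blinding gives 75 patients per arm, which is 150.

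**The concern.** One paragraph gives two per-site figures, 50 and about 38, for practically the same total. With four sites they imply different trials: 200 patients or about 150. The figure of 50 carries no qualifier such as approximately, and it sits in the clause that claims 80% power. The statement on 0.6 fte is argued only from a caseload of 19, which goes with about 38 per site and not with 50. At stake are the recruitment target that sites and funders read from this paragraph, and whether the staffing argument covers the size to which the trial may grow.

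**Working it through.** **Inputs.** Four sites (Participant Population; Training; Appendix A). 1:1 allocation (Treatment Assignment). Aim 150, maximum 200 (Number of Participants). 75 per arm (Randomization, stratification, blinding). The pairs 146 with 50 per site and 147 with about 38 per site, the caseload of 19 and the pilot caseload of 40 (Sample size and power analysis).

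**Per-site arithmetic.** Patients per site = total / 4. Caseload per site = total / 8.

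| Total | Per site | Intervention caseload per site |
|---|---|---|
| 146 | 36.5 | 18.25 |
| 147 | 36.75 | 18.4 |
| 150 | 37.5 | 18.75 |
| 152 (= 4 x 38) | 38 | 19 |
| 200 (= 4 x 50) | 50 | 25 |

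The first four rows agree within rounding with about 38 per site and a caseload of 19. Fifty per site does not: 4 x 50 = 200, which is 54 more than 146 (54/146 = 37%). Conversely, 146/50 = 2.92 sites. The caseload at 50 per site is 25, which is 25/19 - 1 = 32% above the stated 19.

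**Does the power calculation show which figure is the slip?** The inputs from the same paragraph are 3 admissions per year in usual care, 3 x 0.8 = 2.4 under the intervention, 1.5 years of follow-up, 80% power and alpha 0.05. Sidedness is not stated; two-sided is assumed. Poisson variance is used as the most favourable case, since the analysis section plans negative binomial regression but gives no dispersion value.

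- Expected counts: m0 = 3 x 1.5 = 4.5 and m1 = 2.4 x 1.5 = 3.6.
- n per arm = (1.960 + 0.842)^2 x (1/4.5 + 1/3.6) / ln(0.8)^2 = 7.849 x 0.5 / 0.0498 = 78.8, so 79 per arm and 158 in total.
- With 20% attrition: 78.8 / 0.8 = 98.5, so 99 per arm and 198 in total.

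The figure of 146 is not reproduced. Rate-difference and square-root versions give 158 before attrition and 196 to 198 after it. Two other sets of inputs come close. Follow-up of 24 months, two-sided, with division by 0.8 gives 148. Follow-up of 18 months, one-sided, with multiplication by 1.2 gives 148 to 150. Neither set is what the paragraph states.

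**Power by total**, 18 months, two-sided, Poisson, with 20% attrition taken as patients who contribute nothing:

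| Total | No attrition | 20% attrition |
|---|---|---|
| 146 | 77% | 67% |
| 150 | 78% | 69% |
| 200 | 88% | 81% |

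Overdispersion raises the requirement. Adding 2k to the bracket for an assumed dispersion k of 0.25 to 1 gives totals of about 396 to 986 at 18 months with 20% attrition. These values of k are assumptions and only show the direction and range.

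**The case against.** The strongest reply is that this is one stray parenthesis. The totals 146, 147 and 150, the 38 per site, the 75 per arm and the caseload of 19 form a coherent set, and rounding 146 up to an aim of 150 is ordinary. That stands, and it limits the point to the figure of 50.

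Several stronger readings are tempting, but the document does not support them.

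- *Sites would stop recruiting at different numbers.* No section sets a per-site stopping number. The aim and the maximum are trial-wide.
- *It is unclear which total the 80% power belongs to.* The sentence attaches it to 146. Whether 146 delivers that power is a different question.
- *146 against 147 is a second contradiction.* One patient is trivial.
- *Staffing fails at 50 per site, or nurse time per patient falls by a known amount.* A caseload of 25 is still below the pilot's 40. Converting 0.6 fte into hours per patient needs a working week that the Protocol does not give, and it would treat all patients as under equal follow-up at once, although recruitment is staggered and contact falls after three months. The fair statement is that 0.6 fte is argued at 19 and not argued at 25.
- *Fifty per site is a remnant of a three-site plan (3 x 50 = 150), or is the intended figure because 198 is close to 200.* Both are inference. The document gives the origin of neither number.

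**Conclusion.** The inconsistency holds and follows from the Protocol alone. Fifty per site at four sites is 200 patients, 37% above the 146 to which it is attached. It also disagrees with the aim of 150, with 75 per arm and with the caseload of 19. It matters more than a background typing error because it stands in the power statement, yet no analysis, allocation rule or enrolment limit uses it.

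The document does not show which figure should go. From the stated inputs, about 158 patients are needed before attrition and about 198 after it, so removing the 50 without checking could confirm a total that those inputs do not support. These two totals rest on a two-sided test, Poisson variance, and 20% attrition treated as full loss on top of the 18-month median. If the 18-month median is taken to include attrition already, the comparison is 158 against 146. The per-site arithmetic rests on none of these assumptions.

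**What to change.** Rerun the calculation from its stated inputs, with sidedness and the handling of attrition written out. Then give one total with the power that belongs to it, one per-site figure and one caseload, and use them in Number of Participants, Sample size and power analysis, and Randomization, stratification, blinding.

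If the target stays at 150, remove the 50 per site, state about 37 to 38 per site and a caseload of about 19, and restate the power that 150 delivers. Under the assumptions shown in the working this is about 69% with 20% attrition and 78% without, before any overdispersion.

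State separately that the permitted maximum of 200 means 50 per site and a caseload of 25, that this is below the pilot's 40, and whether 0.6 fte is still considered sufficient there.

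Reconciling the figures costs wording only and adds no patients. The rerun may show that the target or its power claim needs revision, which would be a separate decision for the sponsor.

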## Randomization, stratification, blinding

Following informed consent, randomization (75 patients in each arm) will occur via telephone call to a third party (Flinders Medical Centre Research Department, Adelaide), with subsequent selection of opaque, sealed envelopes containing the treatment arm allocation number. To prevent imbalance in disease aetiology, stratified block randomization will be performed for disease aetiology. Strata for alcohol, hepatitis C and “other causes” will occur. With three strata and block sizes of four, the maximum imbalance between treatment groups at the end of randomization will be six, which will not significantly affect statistical power. Blinding of care providers (trial nurses and gastroenterologists) will not be possible with this trial design but outcome assessors will be blinded.

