## Randomisation

The study will be conducted in a randomised controlled manner. Allocation to one of two treatment groups (intervention or control) will occur on a 1:1 ratio across sites and will be stratified by aetiology. A randomisation list will be generated by a statistician and allocations, stratified by aetiology, will be placed into sealed opaques envelopes until randomisation. Upon consent, the CLD nurse will contact an independent researcher at FMC for telephone randomisation. Participant allocation, using unique study ID, will be recorded by the independent researcher and stored in a secure cabinet.

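### The site-held protocol prints one fixed block size of four (a minor, conditional concealment risk), and its maximum imbalance of six bounds only the overall arm totals, not the arms within a site

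*Protocol*

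**What the plan says.** The Protocol's section on randomization, stratification and blinding fixes the scheme. Aetiology is the only factor: "Strata for alcohol, hepatitis C and “other causes” will occur". One block size is given, and an upper limit follows from it: "With three strata and block sizes of four, the maximum imbalance between treatment groups at the end of randomization will be six". The same section says that trial nurses and gastroenterologists cannot be blinded.

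The Randomisation section describes allocation in these terms: it "will occur on a 1:1 ratio across sites and will be stratified by aetiology". It puts the request with the site nurse: "Upon consent, the CLD nurse will contact an independent researcher at FMC for telephone randomisation". The list is prepared by a statistician and kept in sealed opaque envelopes.

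Under the consent section, site investigators or site nurses may approach patients and take consent. Under the role of the CLD nurse, that nurse delivers the intervention. On the number of centres: "This study will be conducted at 4 sites in Australia". The Training section says that a management group including the nurses of all four sites "will initially teleconference weekly for the first two months, then fortnightly-monthly throughout the duration of the project".

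**The concern.** Two things deserve attention.

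1. **Concealment.** With one known block size, anyone who has seen the earlier allocations in a stratum can work out the end of each block. The protocol speaks directly to the nurses in its visit procedures, so they work from the text that prints the number. They are unblinded, may recruit, request the allocation and then care for the intervention patients. If they could foresee an allocation, they could choose whom to approach or when to call. The envelopes exist to prevent that.

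2. **What the six refers to.** A reader who sees 1:1 across sites in one section and a maximum imbalance of six in another may take it that the arms are close to balanced at each site. They need not be. Each site has its own nurse and its own usual care, so within-site comparability is a fair thing for a reader to ask about.

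**Working it through.** **Inputs from the Protocol.** Block size four, three strata, 75 per arm (N = 150), four sites, and about 38 patients per site. The aetiology mix is not given. It was assumed as equal thirds, 60/20/20% and 50/20/30%, and the results hardly moved.

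**The plan's own figure.** An unfinished block of four can leave the arms at most 2 apart. Three strata give 3 x 2 = 6, so the stated maximum reproduces. It also shows that site is not a stratum: 3 x 4 = 12 strata would give 12 x 2 = 24. Relative efficiency at a difference d is 1 - (d/N)^2. At d = 6 this is 1 - (6/150)^2 = 0.998, so the statement that power is hardly affected is also right.

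**Predictability with a stratum's full history known (pooled across sites).**
- Certain allocations: the fourth in a block always, the third when the first two agree (probability 1/3). (1 + 1/3)/4 = 33%.
- Best guess, for a block of 2m: [m + (4^m / C(2m,m) - 1)/2] / 2m. For m = 2: [2 + (16/6 - 1)/2]/4 = 2.833/4 = 70.8%.

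**Predictability with only one site's history known.** The central list is shared by four sites, so a nurse sees about a quarter of each stratum. Simulation gives 52% correct with the simple rule of guessing the arm that is behind. If she also knew the position in the block, she would be about 55% correct and certain for about 2% of allocations. Chance is 50%.

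**Within-site balance under the stated scheme.** If the overall totals are nearly equal, the variance of the arm difference in a site of n patients is about n(1 - n/N). With n = 37.5 this is 37.5 x 0.75 = 28.1, SD 5.3, and a mean absolute difference of 5.3 x 0.80 = 4.2. Simulation gives the same 4.2 and adds:
- a difference of 8 or more in about 15% of sites, and 10 or more in about 7%;
- at least one of the four sites above six in about 56% of trials, and at 10 or more in about 23-24%.

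**Effect of blocks of 4 and 6.** Maximum overall imbalance becomes 3 x 3 = 9, with efficiency 1 - (9/150)^2 = 0.996. In a block of six whose size is known, the certain share is (1 + 0.4 + 0.1)/6 = 25% and the best guess is [3 + (64/20 - 1)/2]/6 = 4.1/6 = 68.3%. Over one block of each size, that is at most (1.333 + 1.5)/10 = 28% certain and (2.833 + 4.1)/10 = 69% correct. When the sizes are not known, the certain share is lower still: two equal allocations at the start of a block no longer settle the third. The gain is therefore mainly in certainty; guessing accuracy falls only a little.

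**Effect of adding site as a stratum.** The mean site difference falls from about 4.2 to 1.2 with blocks of four. A nurse's own-site guessing then rises to about 69% with fixed fours, and is still about 68% with blocks of 4 and 6. With fixed fours, her certain share rises from about 2% to about 30%.

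**The case against.** The strongest reply is that the scheme is sound where it matters. Allocation follows consent and the collection of all baseline data. It comes from an independent researcher holding sealed envelopes, and the Training section keeps the person responsible for randomisation apart from day-to-day management. Investigators as well as nurses may approach and consent patients. The shared list hides the block from any single nurse. The six is correct and is claimed only for the treatment groups overall. All of this stands, and it is why the point is minor.

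Four stronger readings are tempting, but the documents do not support them:
- **That nurses can foresee allocations.** The 33% and 71% need the nurses of four sites to share every allocation, in order and by stratum. The teleconferences make this possible, but nothing says that allocations are discussed there.
- **That site must be a stratum.** Leaving it out is a defensible choice. Adding it improves site balance but makes the list much easier to guess at each site.
- **That caseloads become unworkable.** The sample size section says: "The anticipated caseload of intervention patients per site is 19". Simulated largest caseloads are about 22 (20 to 25). That is above 19, but the same section reports 40 in the pilot.
- **That chance site imbalance biases the result.** It adds noise, which adjustment can reduce. The Statistical methods section already allows covariates, and naming them is commonly left to the analysis plan.

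**Conclusion.** The point holds in a limited form. Disclosing one fixed block size is an avoidable weakness, and its size depends on information sharing: 1/3 certain and about 71% guessable with full pooling, close to chance for a nurse who knows only her own site. The maximum of six is right for the whole trial. It says nothing about sites, where a difference above six somewhere is more likely than not (about 56% of trials), and the 1:1 wording in the Randomisation section can mislead on this.

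The figures rest on 150 patients, four sites of about equal size and an assumed aetiology mix to which the results are insensitive. No error in the power statement or in the choice of strata is implied.

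**What to change.** For the allocations still to be made:
- Have the statistician issue the central aetiology-stratified list with randomly varying block sizes, for example 4 and 6.
- Take the block size out of the protocol and record it in a document that the sites do not hold.
- Reword the imbalance sentence to say that the maximum applies to overall arm totals and not within sites. With blocks up to six it is 9. If stating 9 would reveal the largest block, put the figure in the restricted document too.
- Say in the Randomisation section that 1:1 across sites means the trial as a whole and that site is not a stratum.

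Do not add site as a stratum by default, for the reason shown above. Chance site differences can be handled by including site and aetiology stratum in the primary model. The protocol already permits this, and it also covers patients already randomised.

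The cost is a new list, new envelopes and a few sentences, plus a slightly larger possible overall imbalance (9 instead of 6, efficiency still 0.996). The planned timeline and the COVID-19 recruitment text suggest that many patients may already be randomised. The new list may therefore affect few allocations, but the wording change is useful in any case.

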## Statistical methods

All analyses will be performed according to an intention-to-treat protocol. Differences between groups for hospitalization rates, quality indicators, satisfaction rates and self-management scores will be assessed using negative binomial regression, which is appropriate for count data with evidence of over-dispersion. All models will allow adjustment for baseline values and other co-variates. Suitable transformations will be applied in the case of non-normally distributed data.

For the economic analysis mean costs between the intervention and control groups will be compared and incremental cost effectiveness ratios presented with confidence intervals. Cost effectiveness acceptability curves for varying threshold values of cost effectiveness will also be presented ([46](#_ENREF_46)). An assessment of the sensitivity of the results obtained to variation in measured resource use, effectiveness and/or unit costs will be undertaken using appropriate one-way and multi-way sensitivity analysis ([47](#_ENREF_47)). Differences between groups in quality of life scores will be assessed using mixed effects regression to account for the repeated measures (every 3 months) and subsequent within-Participant correlation. Survival analysis will be performed using Cox regression with results presented as Kaplan-Meir survival curves.

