## Secondary Objectives

- To evaluate incremental cost effectiveness for this intervention, relative to usual care. Assessment of quality of life will be a necessary component of the economic analysis. The QALY will be used to assess this outcome.
- To evaluate the effect of CDM on mortality
- To evaluate the effect of CDM on the quality of care provided to patients in the intervention arm. This will be assessed using the following measures:
  - attendance at planned outpatient care;
  - medication adherence;
  - adherence to antibiotic prophylaxis protocols for patients with ascites;
  - adherence to variceal bleeding prevention protocols;
  - adherence and response to alcohol abuse treatment protocols in alcoholic liver disease patients; and
  - referral rates to liver transplantation assessment teams.
- To compare self-management ability and knowledge of patients in the CDM arm with usual care models.

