## Patient Satisfaction and Self-Management Ability

The following surveys will be administered at baseline, 3 months, 6 months and then 6-monthly and at the end of the trial:

- PIH - The Partners in Health (PIH) scale to assess changes in patient self-management ability ([45](#_ENREF_45)).
- A local disease specific knowledge assessment questionnaire, the “Cirrhosis Knowledge Assessment Questionnaire”.
- The ASK-12, a medication adherence tool will be used to determine medication adherence
- A Satisfaction Survey will be administered at the end of the study in both groups.

Qualitative feedback from patients will also be sought at the end of trial via a telephone interview with a researcher not directly involved in the patient’s care. Although consent for inclusion in the interview will be sought at the start of the trial, patients will be given the chance to ‘opt out’ if they are approached to participate and decide that they do not wish to. After the interview if patients feel they wish to change their answer or review their answer, a number will be provided so they can do so within a certain time.

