## Appendix C – Ascites and Hepatic Encephalopathy Assessment

**Timepoint Assessment Completed:**  Baseline (intervention only) - Date: ___ / ___/ __

End of Trial - Date: ____ / ____/ _____

| ***ASCITES*** | | **Yes** | **No** |
| --- | --- | --- | --- |
| 1 | Does the patient have or ever had ascites?  If yes, add to care plan and continue with questions below.  If no, go to HE assessment. |  |  |
| 2 | If yes, is the patient on diuretics? (if yes, add to medication chart) |  |  |
| 3 | Action Plan given to patient and discussed |  |  |
| 4 | Weight chart discussed |  |  |
| 5 | Does patient have digital scales? (if no, add to care plan) |  |  |
| 6 | Any prior episode of spontaneous Bacterial Peritonitis (if yes, add to Care Plan) |  |  |
| 7 | Any evidence of prior total protein level in ascitic fluid ≤ 10g/L? |  |  |
| 8 | Is patient prescribed SBP prophylaxis? (If yes, add to medication list) |  |  |

Comments:

| ***HEPATIC ENCEPHALOPATHY*** | | **Yes** | **No** |
| --- | --- | --- | --- |
| 1 | Has patient ever had diagnosis of HE? (If yes, add to care plan and continue with below) If no – go to question 6. |  |  |
| 2 | Is patient on lactulose? (ensure on medication chart) |  |  |
| 3 | Is patient on rifaxamin? (ensure on medication chart) |  |  |
| 4 | Action plan for HE discussed |  |  |
| 5 | Does the patient drive? (if yes, ensure fitness to drive reviewed) |  |  |
| 6 | Number connection test done SCORE: ________________ seconds |  |  |
| 7 | EncephalApp assessment done SCORE: ___________________ |  |  |
| 8 | Does the patient have minimal HE? |  |  |

Comments:

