## Appendix F – Variceal Management Assessment

**Timepoint ASSESSMENT COMPLETED:**  Baseline - Date: ____ / ____/ _____

End of Trial - Date: ____ / ____/ _____

| ***VARICES*** | | **Yes** | **No** |
| --- | --- | --- | --- |
| 1 | Has the patient had an Endoscopy? (if no, add to care plan to refer for screening) |  |  |
| 2 | Has the patient ever had a variceal bleed? (If yes, add to care plan) |  |  |
| 3 | Confirm education given regarding variceal bleeding cause and prevention |  |  |
| 4 | Assessment of eligibility for Baveno VI Criteria  Fibroscan < 25kPa – Date fibroscan done __ / __ / ____  Platelets > 110 – Platelet level ______ Date __ / __ / ____  If fibroscan not done, ensure this is on the care plan |  |  |
| 5 | What was the date and outcome of the most recent endoscopy?  Date: ____ / ____/ _____  No varices  Small varices (<5mm, or Grade 1 or 2)  Large varices/High risk varices (>5mm, or Grade 3)  No endoscopy done  Endoscopy not required due to Baveno VI criteria |  |  |
| 6 | According to the outcome above and the protocol for variceal screening and surveillance, what is the plan of care? (ensure add to care plan and recalls)  Baveno VI criteria – fibroscan due ____ / ____ /_______  Endoscopy in 3 years due ____ / ____ /_______  Endoscopy in 2 years due ____ / ____ /_______  Endoscopy in 1 year due ____ / ____ /_______  Variceal Ligation (eradication) ____ / ____ /_______  TIPS done ____ / ____ /_______  Primary prophylaxis (please add to medication chart and care plan)  Secondary prophylaxis post variceal bleed (please add to medication chart and care plan) |  |  |
| 7 | Was the patient adherent to variceal bleeding prevention protocols (answer only at end of trial) |  |  |
| 8 | Prophylaxis – primary or secondary  What is the patient’s pulse rate? ____________ bpm  (ensure that the patient is resting comfortably for 10 minutes prior to taking pulse rate) |  |  |

Comments:

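### Negative binomial regression is fixed for quality indicators recorded as one Yes/No per patient, where its model-based standard errors are too large; repeated self-management scores are given no within-patient term

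*Protocol*

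**What the plan says.** The Protocol, under Statistical methods, puts four kinds of outcome under one model: "Differences between groups for hospitalization rates, quality indicators, satisfaction rates and self-management scores will be assessed using negative binomial regression". The reason given is that this model is one "which is appropriate for count data with evidence of over-dispersion". The section also allows adjustment for baseline and other covariates, and transformation of non-normal data. For one group of outcomes only it plans a repeated-measures model: "Differences between groups in quality of life scores will be assessed using mixed effects regression to account for the repeated measures".

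The quality indicators are listed under Secondary Objectives. They include "adherence to antibiotic prophylaxis protocols for patients with ascites", adherence to variceal bleeding prevention, medication adherence, outpatient attendance and "referral rates to liver transplantation assessment teams". The collection forms show how some of them are recorded:

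- Appendix F, Yes/No columns: "Was the patient adherent to variceal bleeding prevention protocols (answer only at end of trial".
- Appendix C, Yes/No columns: "Is patient prescribed SBP prophylaxis? (If yes, add to medication list".
- Appendix K: each outpatient appointment is ticked as attended or not.

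On the PIH, knowledge and ASK-12 instruments, the section Patient Satisfaction and Self-Management Ability says "The following surveys will be administered at baseline, 3 months, 6 months and then 6-monthly and at the end of the trial". The activity schedules place five surveys at baseline and at months 3, 6, 12, 18 and 24. The baseline list names these three instruments together with the quality-of-life instruments CLDQ and EQ-5D-5L.

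**The concern.** The Protocol states its own condition for the negative binomial model, and a Yes/No item fails it. A 0/1 variable has variance p(1-p), which is always below its mean p, so there is no extra-Poisson variation to model. The fit falls back to its Poisson limit, which assigns variance p where the true variance is p(1-p). Confidence intervals are then too wide and tests too conservative, most of all when adherence is common.

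The repeated scores raise a different question. They have the same visit structure as quality of life, but the sentence that governs them contains nothing for correlation within a patient.

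The Quality of care indicators section presents the indicators as process measures of whether the intervention was implemented and worked. They will be used to interpret the primary result, whether positive or null. An apparent absence of change in care could come from the model rather than from the trial.

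**Working it through.** **Inputs.** 75 per arm (Randomization, stratification, blinding); 20% attrition, hence 75 x 0.8 = 60 per arm (Sample size and power analysis); alpha 0.05, taken as two-sided because sidedness is not stated. The Protocol gives no adherence rate and no within-patient correlation, so every such value below is an assumption. It also states no power for these outcomes, so there is no figure of its own to reproduce; the 146 belongs to the primary endpoint.

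**1. Inflation for a Yes/No item with the same rate p in both arms.** Poisson-limit SE of the log risk ratio = sqrt(2/(np)); correct SE = sqrt(2(1-p)/(np)). The ratio is 1/sqrt(1-p). The true two-sided error of a nominal 5% test is 2[1 - Phi(1.96/sqrt(1-p))].

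| Assumed p | SE ratio | True error |
|---|---|---|
| 10% | 1.05 | 0.039 |
| 20% | 1.12 | 0.028 |
| 60% | 1.58 | 0.002 |
| 80% | 2.24 | 0.00001 |

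**2. One illustrative data set: 36/60 versus 48/60.**
- Poisson limit: ln(0.8/0.6) = 0.288; SE = sqrt(1/36 + 1/48) = 0.2205; z = 1.30; p = 0.19.
- Logistic: ln(4/1.5) = 0.981; SE = sqrt(1/36 + 1/24 + 1/48 + 1/12) = 0.4167; z = 2.35; p = 0.019.

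**3. Power.** SE_P = sqrt(1/(n p0) + 1/(n p1)) is what the prescribed model reports. SE_B = sqrt((1-p0)/(n p0) + (1-p1)/(n p1)) is the true sampling SE. Power is Phi[(ln RR - 1.96 SE_P)/SE_B] under the prescribed model and Phi[(ln RR - 1.96 SE_B)/SE_B] under a binomial model.

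| Assumed rates | n per arm | SE_P | SE_B | Prescribed | Binomial |
|---|---|---|---|---|---|
| 60% v 80% | 75 | 0.197 | 0.111 | 19% | 74% |
| 60% v 80% | 60 | 0.220 | 0.124 | 12% | 64% |
| 10% v 25% | 75 | 0.432 | 0.400 | 57% | 63% |

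A simulation of the Poisson-limit test at 60% versus 80% with 75 per arm rejected in 18% of runs, against 77% with the binomial variance. With 60% in both arms the figures were 0.4% and 4.7%.

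**4. Repeated scores, if all five follow-up visits were pooled with no within-patient term.** Simulated null rejection was 20%, 25% and 32% at assumed correlations of 0.3, 0.5 and 0.7. A design-effect check agrees. The variance is understated by 1 + 4 rho, which is 2.2, 3.0 and 3.8, so the true error 2[1 - Phi(1.96/sqrt(1 + 4 rho))] is 0.19, 0.26 and 0.31. Here standard errors are too small, the opposite of step 1.

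**5. One score at a single time.** On a simulated 0-96 scale (assumed mean 70, SD 15), power was 0.81 with negative binomial and 0.82 with a linear model; null rejection was 0.058 and 0.060. The harm is negligible.

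**The case against.** A reader might infer that the prescribed model hides real differences in every outcome the sentence names. The documents do not support that.

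- **Repeated scores.** Ignoring correlation produces false positives, not missed effects. Even that depends on pooling the visits, which the Protocol does not state. Its allowance for baseline adjustment fits an end-of-study comparison equally well, and step 5 shows that such a comparison is little affected.
- **Satisfaction.** The survey is given once and its format is not shown, so nothing can be said about whether the model suits it.
- **Attendance.** This can be treated as a count with an offset for planned appointments. In simulation (70% versus 80% attended, 4 to 13 appointments, 75 per arm), negative binomial against a binomial model with robust variance had power of 60% against 99% with no variation between patients, 55% against 72% with moderate variation and 52% against 57% with strong variation. It is defensible if patients differ strongly.
- **Size.** The large losses occur at high adherence. For uncommon items, as transplant referral may be, the loss is small. Denominators will also be lower than 75 for some items: SBP prophylaxis concerns only patients with ascites, and the variceal item is answered only at the end of the trial.
- **Variance estimator.** The inflation assumes model-based variance. With zero dispersion and a robust variance, the prescribed model would be the robust Poisson model recommended below.

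These points limit the scope but leave the core standing. The Protocol does not call for robust variance, and neither covariate adjustment nor transformation can make a Yes/No item over-dispersed.

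**Conclusion.** The point holds for Yes/No quality indicators: the Protocol fixes a model whose stated condition these items cannot meet. With model-based variance, the standard error is too large by 1/sqrt(1-p). That is a few percent for an uncommon item and a factor of about 2 at 80% adherence. The power loss at 75 per arm ranges from 6 percentage points (10% versus 25%) to about 55 (60% versus 80%), all at assumed rates.

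For PIH, knowledge and ASK-12 the finding is narrower. Instruments on the same schedule are treated differently without a reason, and pooling would raise the false-positive rate to roughly 20-32% at the assumed correlations. ASK-12 falls under the sentence through medication adherence and PIH through self-management. Knowledge is not named in it, but it shares their section and schedule.

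No claim is made about satisfaction. The primary outcome is an admission count, for which negative binomial regression is suitable, so only secondary outcomes are affected. The sponsor should change the wording before analysis.

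**What to change.** Replace the single sentence with a model for each outcome type:

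- **Admissions and bed days:** keep negative binomial regression, with log person-time as offset.
- **Yes/No indicators:** logistic or log-binomial regression, or Poisson regression with robust variance if a risk ratio is wanted. State the denominator for each indicator, for example patients with ascites for SBP prophylaxis.
- **Attended out of planned appointments:** a binomial model that allows over-dispersion between patients.
- **PIH, knowledge and ASK-12:** extend the mixed-effects model already planned for quality of life, with baseline as covariate.

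The cost is one paragraph of Protocol or SAP wording. No new data, visits or patients are needed, and the primary analysis does not change.
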